#### Neural activation in response to reward measured with fMRI

The fMRI data acquisition will take place at the Department of Nuclear Medicine at the University Hospital Zurich. To measure brain structure and function, we use a 3.0-Tesla whole-body scanner. The measures include T1-weighted images (structural MRI)
Resting state functional MRITask free: Subjects are instructed to just lie quietly in the scanner and to think of nothing in particular and let their mind wander.Task-based functional MRI during the reward taskTotal time in the scanner will be about 45 min.

#### Reward task (wheel of fortune task) (adapted from [5])

The subjects will perform a reward task adapted from a version of a wheel of fortune task [5], to measure reward during fMRI. The task consists in a computer screen showing a wheel of fortune presented to the participants (see Fig. 2). The wheel has four sections of the same size but with four different colors. The task is composed of two types of trials. There are rewarded and neutral trials. In the first ones, participants can choose between the four colors of the wheel and then press the corresponding button, and they will receive a large or a small monetary reward on a pseudo-randomized schedule every third time in average. In the second type of trials, participants can choose between the four colors of the wheel and then press the corresponding button, but receive no feedback on their answer. In both conditions, after pressing the button, the wheel starts spinning and then stops and the cursor indicates a color. In the reward condition, there are two possibilities: if the cursor indicates the color chosen by the participant, the participant wins some money; if it does not stop on the selected color, the participant wins no money. For the “neutral” condition, the cursor shows any color, but there is no feedback. The participants are informed about the different types of trials with the presentation of a cue information at the beginning of the trial. The subjects are instructed that they will receive the sum shown at the end of the experiment. The subjects will be asked to rate their mood with a visual analog scale in regular intervals. A short training of the task will take place before the beginning of the scanning session outside and inside the scanner. The outcome is the difference in neural activation before and after the 8-week MORE intervention. We will compare neural activation related to reward at pre-test and at post-test between the FMS participants of the MORE group and the participants of the waitlist.

**Fig. 2 Fig2:**
[figure not shown]
The reward task wheel of fortune

#### Ambulatory assessment measures and physiological measures

To investigate the effects of the MORE intervention on daily affects, stress, and reward experiences, we will use ambulatory assessment (AA) measures. Primary outcomes related to the AA measures include (1) self-reported measures of pain; (2) self-reported measures and physiological measures (CAR, alpha-amylase awakening, and daily profile of cortisol and alpha-amylase) of stress, (3) measure of positive affect, and (4) measures of reward experience. They will be compared between FM participants and healthy controls before the MORE intervention and before and after the MORE intervention between both FM groups. AA self-reports of pain, stress, and reward and positive experiences in daily life will be performed using an adaption of the Experience Sampling method [71] to assess the stress and reward experience in the daily living environment. The items related to pain are defined according to a pain diary that we have developed, tested, and validated in 50 chronic pain patients at the University of Fribourg. The self-reported items measuring stress, positive and negative affects, and reward experiences have additionally been adapted and validated in the framework of another research project [41]. All self-assessments are rated on a 7-point Likert scale. The participants will receive an iPod and perform self-assessments during 5 weeks five times a day, during the week preceding or following the PET measures before and after the MORE intervention. At the end of each day, participants randomly assigned to MORE will record the number of minutes spent engaged in the mindfulness, reappraisal, and savoring practices taught in the MORE intervention to provide a measure of adherence with the home practice associated with the MORE training. Biological measures of stress in everyday life will be assessed by collecting saliva samples 6 times a day (2 for cortisol awakening response (CAR) and for the salivary alpha-amylase (AA) awakening, 4 for daily profile) for a total of 3 days. Saliva samples will be obtained by using the passive drooling method (Salicap, IBL International Hamburg, Germany). Saliva samples will be stored overnight in the participant’s refrigerator. The saliva samples will be then sent to the Department of Psychology at the University Fribourg, where they will be stored at −20 °C in a freezer dedicated to research with restricted access. The CAR resp. AA awakening profile and the daily profiles will be used as biological indexes of stress reactivity in everyday life [71]. The outcome is the difference between pre-test and post-test and the comparison between the MORE group and the waitlist group. All samples will be sent for analyses at the end of the study.

#### Follow-up measures

Follow-up measures include all questionnaires presented online via RedCAP, 3 months after the end of MORE intervention (+ 20 to + 24 weeks after MORE beginning for the non-intervention control group).

### Plans to promote participant retention and complete follow-up {18b}

Participation in this study is voluntary. If a participant wishes to retain from participating, she can stop the study without justification. In case of withdrawal, the biological materials and health-related data collected before withdrawal will be stored and analyzed in coded form and used in the analyses.

### Data management {19}

All study data must be archived for a minimum of 10 years after study termination or premature termination of the clinical trial. Study data will be archived at the University Fribourg.

For data recording, we will use electronic case report forms (eCRF) from REDCap which are available at the University Hospital Zurich, University Fribourg, and at the CHUV. For each participant, an individual CRF is maintained. The CRF is coded for each participant with protocol identifier plus randomization number based on the guidelines for an acceptable coding of trial subjects available on www.swissethics.ch. Source data in this study is all information in original records, certified copies of original records of clinical findings, questionnaires, observations, or other recorded activities collected during the study only. All collected data during the study will be transferred to the participant’s CRF. Direct access to source documents will be permitted for purposes of monitoring, audits, or inspections. Access to the project plan, dataset, and statistical code, during and after the research project (publication, dissemination), will be determined by the PI. Coding will be done using participant numbers and participants will be given a number in a chronological order with the first number differentiating between healthy controls and FM participants in the screening log. Data exchange between the centers will be done using coded data. For interim and for the main analyses, the (coded) data of the study centers will be merged into one file to perform the analyses.

### Confidentiality {27}

The investigators are liable to treat the entire information related to the study and the compiled data strictly confidential. Any passing-on of information to persons that are not directly involved in the study must be approved by the owner of the information. Direct access to source documents will be permitted for purposes of monitoring, audits, and inspections. Data generation, transmission, archiving, and analysis of personal data within this study strictly follow the current Swiss legal requirements for data protection. Prerequisite is the voluntary approval of the participant given by signing the informed consent prior start of participation of the clinical trial. Individual participant medical information obtained as a result of this study is considered confidential and disclosure to third parties is prohibited. Participant’s confidentiality will be further ensured by utilizing participant identification code numbers to correspond to treatment data in the computer files. Such medical information may be given to the participant’s personal physician or to other appropriate medical personnel responsible for the participant’s welfare, if the patient has given his/her written consent to do so. Data generated as a result of this study are to be available for inspection on request by the monitors and by the Cantonal Ethics Committee.

### Plans for collection, laboratory evaluation, and storage of biological specimens for genetic or molecular analysis in this trial/future use {33}

Biological specimens obtained under this protocol will be stored in coded form (protocol identifier plus randomization number), in freezers located in an access-controlled room at the University Fribourg. The cooling of the freezer system is guaranteed as an increase in temperature will lead to an alarm that goes directly to the PI’s designee’s phone or any other predetermined person in charge for the cooling system. When coded data is shared, the key to the code will not be provided to collaborators, but will remain in the hands of the PI and her designees. Saliva samples will be collected in coded form and sent to the Department of Psychology at the University Fribourg with a prepared envelope for storage. Coded saliva samples for cortisol and amylase analyses will be frozen and stored at −20 °C in a freezer located in the access-controlled room at the University Fribourg. After collection of saliva samples from all participants, the samples will be shipped to the Dresden Lab Service located at the University of Dresden, an institution operating under the Declaration of Helsinki.

Saliva samples will be destroyed from the laboratory after the analyses. If a participant withdraws from the study, all collected data will be kept and used for data analyses.

## Statistical methods

### Statistical methods for primary and secondary outcomes {20a}

#### Planned analyses

In general, the main analyses will follow a 2-factorial design treatment group (FM MORE intervention group and FM non-intervention control) × time (pre-test and post-test) for the main analyses comparing the pre-test and post-test measures in the FM participants having participated in the MORE intervention versus the FM participants of the non-intervention control. These analyses will be done with ANOVA’s for the questionnaires, pain threshold measures, and CAR measures as well as for extracted 18F-DOPA influx estimate parameters and beta values for the fMRI analyses. AA self-report measures will be computed as means and analyzed with ANOVA’s. For analyses related to follow-up, we will include a third level (follow-up) to the time factor.

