#### Main secondary outcomes

2)The percent BOLD signal change in striatal activity during the reward task: the difference between FM patients and healthy controls at pre-test and between pre-test and post-test in FM patients3)The correlation between daily practice of mindful breathing and savoring (minutes) and increased striatal activity and 18F-DOPA influx4)Changes in pain-related and other clinical outcomes: the difference between FM patients-healthy controls at pre-test and between pre-test and post-test in FM on scores of quality of life (WHOQOL Brief [62];) and mood disturbances (State-Trait Anxiety Inventory (STAI [48];), Beck Depression Inventory (BDI)-II [43], Fibromyalgia Impact Questionnaire (FIQ [7];), Pittsburgh Sleep Quality Index (PSQI; [14]), and Emotion Regulation Questionnaire (CERQ; [51])5)Effects of the MORE intervention on self-reported pain, positive affect, and stress in daily life measured with AA: the difference between FM patients and healthy controls at pre-test and between pre-test and post-test in FM patients

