### Sample size {14}

Sample size justification:

The power analysis for the primary outcome is based on the following results:

• A study comparing 18F-DOPA influx between FM participants (*N* = 6) and a healthy control (*N* = 8) group [74, 75] yielded a mean effect size of 1.17; using this effect size, a power analysis with G*Power [19] showed that a group of 12 participants is optimal to obtain significant results with *T*-test comparing 18F-DOPA uptake between FM and healthy participants at baseline. We would round up to 20 to accommodate for technological problems, as the first measures will be done in healthy participants.

• Garland et al. [32] found significant neurophysiological changes after MORE treatment with EEG measure in 29 participants (F1,26 = 4.47; ηpartial^2^ = .15) in response to reward before and after the MORE intervention in chronic pain patients with sample sizes of *N* = 11 (active group) and *N* = 18 (support group). Using this effect size, a power analysis with G*Power [19] showed that 14 participants are necessary for an ANOVA with 2 factors and repeated measures to be significant. However, results obtained with EEG cannot be directly compared to PET measures, and there are so far no available studies with FDOPA in that context.

The power analysis for the secondary outcomes is based on the following results:

• A randomized controlled study of the MORE intervention by Garland et al. [26, 31] evidenced significant reductions in self-reported pain severity with medium effect size (Cohen’s *d* = 0.5, effect size *F* = 0.46) after the MORE intervention in a starting group of 115 participants and of 69 at post-intervention measures (*N* = 31 for MORE and *N* = 38 for support group). Based on these estimates, an ANOVA to be significant should have a minimal sample of *N* = 20 participants after treatment in each group.

• A randomized controlled study by Garland et al. [33–35] found significant effects of MORE on self-reported pain, stress, and positive affects in daily life (with AA measures) in a group of *N* = 30 using multilevel analyses, with effect sizes yielding to a minimal sample of 20.

• In their randomized clinical trial of the MORE intervention in chronic pain patients with opioid abuse, [26, 31] found a 20% drop-out between the beginning and completion of the intervention.

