#### Secondary analyses

##### Secondary outcome: neural responses to reward

The reward task will be performed in the fMRI scanner, and we will correlate the 18F-DOPA influx with the striatal activation obtained with the fMRI task. In order to measure the behavioral differences in the fMRI task results, in the ambulatory assessment data, and in the intervention program’s efficacy between the groups tested, we plan to use different kinds of variance analyses and multilevel analysis. The number of participants for each part of the study has been determined in order to assure a good statistical power according with this specific research domain (e.g., including potential dropout, outliers). fMRI data analysis will be performed with state-of-the art software freely available online. T1-weighted scans will be analyzed with regard to cortical thickness and subcortical volumes using surface-based morphometry implemented in FreeSurfer software suite 5.0.1 (http://surfer.nmr.mgh.harvard.edu). This includes a fully automated method. Briefly, this processing includes (1) motion correction, (2) removal of non-brain tissue, (3) automated Talairach transformation, (4) segmentation of the subcortical white matter and deep gray matter volumetric structures (amygdala, hippocampus, thalamus, caudate, putamen, pallidum, nucleus accumbens, ventricles), (5) intensity normalization, (6) tessellation of the gray matter/white matter boundary, (7) automated topology correction, and (8) surface deformation following intensity gradients to optimally place the gray/white and gray/cerebrospinal fluid borders at the location where the greatest shift in intensity defines the transition to the other tissue class. Freesurfer morphometric procedures have been demonstrated to show good test-retest reliability across scanner manufacturers and across field strengths. Obtained subcortical volumes will be normalized by individual intra-cranial volumes for further statistical analysis. Exploratory approaches will involve a vertex-based analysis across the whole brain. Diffusion MRI scans will be analyzed for structural connectivity with FMRIB software library 4.1.9 (FSL, http://fmrib.ox.ac.uk/fsl). Functional MRI scans will be analyzed for activity and functional connectivity with the latest version of Statistical Parametric Mapping (SPM, http://www.fil.ion.ucl.ac.uk/spm). Functional MRI data will be pre-processed according to the following steps: (1) slice timing correction, (2) realignment, (3) linear and non-linear normalization onto a standard EPI template, (4) voxel re-sampling to 2×2×2 mm^3^, (5) smoothing with a Gaussian kernel of 6 mm full width at half maximum, (6) detrending, (7) filtering (such that frequencies 0.01 < *f* < 0.08 Hz passed the filter), and (8) regressing out the variance of nuisance covariates. With REST toolbox 1.6, for each subject and each specified region of interest (atlas-based specification), mean signal time courses will be extracted and cross-correlated. Next, correlations will be *r*-to-*z* transformed for group-level statistics. These *z*-values can be used for comparisons across (cross-sectional) and within (longitudinal) groups or for parametric correlations with psychometric measures. A region-of-interest approach will be used in subcortical regions involved in reward to obtain beta-weights (parameter estimates) that can be correlated with the 18-FDOPA estimate parameters as well as with AA self-report means and other outcomes.

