##### Secondary outcome: daily affect, reward, stress, and pain experience

The AA measures yield intensive longitudinal data that are clustered, as they represent series of measurements that stem from different individuals. A multilevel approach to analyze these data takes into account clustering and can therefore accommodate these data and provides flexible tools to investigate within-subject phenomena, such as responses to stressors or rewarding experiences (see [9]). Data will be analyzed with a software that allows for the simultaneous modeling of within-subject and between-subject aspects of the data, and the examination of associations among individual difference variables, and individual differences in within-subject parameters (e.g., Mplus 7.3 (Muthen & Muthen, [55]-2012) or HLM software). To correlate these measures with the 18FDOPA uptake values, mean values for the AA measures will be computed.

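### Ambulatory self-reports are given two unranked analyses, ANOVA on person means and multilevel modelling, so the test of the group × time effect is left open

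*Protocol article*

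**What the plan says.** Four places in the protocol article bear on how the ambulatory assessment (AA) self-reports are analysed.

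- **Planned analyses (item 20a).** After setting out the treatment group × time design for the main analyses, the text says "AA self-report measures will be computed as means and analyzed with" ANOVAs.
- **Secondary outcome: daily affect, reward, stress, and pain experience.** This is the outcome's own section. It says "A multilevel approach to analyze these data takes into account clustering and can therefore accommodate these data". Person means appear once, for another purpose: "To correlate these measures with the 18FDOPA uptake values, mean values for the AA measures will be computed".
- **Secondary outcome: neural responses to reward.** For behavioural fMRI results, the ambulatory data and the programme's efficacy together, "we plan to use different kinds of variance analyses and multilevel analysis".
- **Sample size (item 14).** The AA requirement is taken from an earlier MORE trial that found effects "using multilevel analyses, with effect sizes yielding to a minimal sample of 20".

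The status of the outcome is clear. "Effects of the MORE intervention on self-reported pain, positive affect, and stress in daily life measured with AA" is the fifth item under Main secondary outcomes.

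On missing data, item 20c keeps everyone with pre-test measures and carries the last observation forward. The Discussion repeats that rule and adds that complete datasets are analysed first and then compared with the intent-to-treat result.

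**The concern.** An ANOVA on person means and a multilevel model on momentary ratings can give different p-values for the same group × time contrast. They weight women differently: the ANOVA counts a woman with a few answered prompts as much as one who answered nearly all. They also treat a missing post-test diary differently. If both are stated and neither is designated, the deciding test can be settled once results are known. Staff and participants are unblinded (item 17a), and the AA section lists several self-report domains, so the choice arises more than once.

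At stake is the credibility of a secondary claim about daily life. The 18F-DOPA and questionnaire outcomes are not affected.

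**Working it through.** **1. The texts side by side.** Planned analyses reduces AA ratings to means and tests them by ANOVA. The outcome's own section models the momentary data and reserves means for correlation with 18F-DOPA. The fMRI section lists both families with no order. No sentence says which one decides, so this is a conflict in what is stated and not a missing detail.

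**2. The plan's own figures.** No power figure is given for the AA test, and the effect size behind its minimal sample of 20 is not reported, so that number cannot be reproduced. The drop-out inflation can: 20 / (1 − 0.20) = 25 per group, as stated, then rounded up to 32. At 20% loss, 0.20 × 32 = 6.4 women per arm (12.8 of 64) would have no post-test diary.

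**3. Weighting.** The variance of a woman's period mean around her own level is σ²(period) + σ²(moment) / k, with k answered prompts. Assume SDs of 0.5 and 1.2:
- k = 3: 0.25 + 1.44 / 3 = 0.73
- k = 35: 0.25 + 1.44 / 35 = 0.29

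ANOVA on means weights the two equally; the multilevel model does not.

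**4. Missing post-test diaries.** With LOCF on means, a woman without a post-test diary contributes a change of exactly zero. If 20% are lost at random and the true difference is 0.5, the expected estimate is 0.80 × 0.5 = 0.40. The multilevel model uses her pre-test prompts and imputes nothing.

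**5. Simulation.** From the document: 32 per arm and 20% without post-test. Assumed: between-person SD 1.0, momentary SD 1.2, and the values in the table. There were 4,000 runs with no effect and 2,000 with a difference of 0.5. The multilevel model had a free baseline and known variance components, which favours it a little.

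| Setting | Complete-case ANOVA | LOCF ANOVA | Multilevel | Complete-case ANOVA or multilevel | LOCF ANOVA or multilevel | Any of three |
|---|---|---|---|---|---|---|
| **No effect: rejection rate** | | | | | | |
| A: 35 prompts, compliance 30–100%, period SD 0.5 | 0.049 | 0.050 | 0.042 | 0.058 | 0.059 | 0.061 |
| B: 35 prompts, compliance 5–100%, period SD 0.3 | 0.059 | 0.057 | 0.047 | 0.073 | 0.072 | 0.075 |
| C: 25 prompts, compliance 10–100%, period SD 0.5 | 0.052 | 0.052 | 0.045 | 0.064 | 0.064 | 0.066 |
| **Difference 0.5: power** | | | | | | |
| A | 0.58 | 0.57 | 0.59 | | | |
| B | 0.70 | 0.68 | 0.79 | | | |
| C | 0.46 | 0.46 | 0.50 | | | |

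The Monte Carlo standard error is √(0.05 × 0.95 / 4000) = 0.003 for a 5% rate and about √(0.5 × 0.5 / 2000) = 0.011 for power.

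With a period SD of 0.6 and 35 prompts, power was 0.42–0.46 for either ANOVA and 0.47–0.48 for the multilevel interaction, depending on the spread of compliance. Either-test rejection under no effect was 0.05–0.07, against 0.04–0.06 for one test.

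**6. Prompt count.** The AA section gives the diary period both as 5 weeks and as the week before or after PET. Thirty-five prompts is 7 days × 5; 25 is 5 days × 5. Both are assumptions.

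**The case against.** The best defence is that the two analyses answer different questions: ANOVA on means for the average treatment effect, and multilevel models for within-person processes such as responses to stressors. The outcome's section does mention within-subject phenomena and never writes out a multilevel group × time test. That reading is possible, but the protocol does not state it. The same section presents the multilevel approach as the way to analyse these data, and the fMRI section names both families for the ambulatory data and programme efficacy together. If a split is intended, one sentence should say so.

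The sample-size reference is weak evidence either way. It describes how an earlier trial was analysed and does not fix this trial's test.

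Three stronger readings are tempting but not supported:

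- **That two confirmatory tests compete.** No section gives the AA analyses confirmatory status. The outcome is secondary, and the Discussion concedes that proper AA analyses need larger samples and speaks of exploratory analyses. The wording about primary outcomes in the AA section ranks measures within that domain.
- **That the ANOVA discards women without post-test diaries.** Item 20c keeps them through LOCF. They fall out only in the complete-dataset run described in the Discussion, which applies to analyses generally and is compared with intent-to-treat.
- **That the ANOVA costs substantial power.** In the period-SD 0.6 setting, the multilevel model reached 0.52–0.54 only when baseline means were forced equal, which is a different model from a group × period interaction. Otherwise a gap of about ten points needed very uneven compliance (setting B).

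A statistical analysis plan could supply the model hierarchy, so its absence here is no fault. Two conflicting statements in the protocol are.

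**Conclusion.** The point holds as an unresolved conflict over which analysis decides the group × time effect for the ambulatory self-reports. The inflation is modest: about 5–7% per outcome instead of about 5% if either ANOVA or the multilevel model may be chosen, and up to about 7.5% if the complete-case and LOCF versions of the ANOVA are both open. The multilevel model's power advantage ran from about 1 to 10 percentage points and was small unless compliance was very uneven. Its clearer merit is that it avoids the zero-change assumption of LOCF. The error rates and power rest on assumed variance components, compliance and prompt counts that the document does not give; the conflict itself rests on the text alone. It is worth correcting, and it does not touch the primary outcomes.

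**What to change.** - In the section on daily affect, reward, stress, and pain experience, name the multilevel model with the group × period interaction, fitted to all available prompts (prompts within period within woman), as the single decisive analysis of each ambulatory self-report.
- In Planned analyses, delete the sentence on ANOVA of AA means or label that analysis a sensitivity analysis.
- In the fMRI section, align the sentence naming both families, so that it no longer leaves the ambulatory test open.
- Keep person means for the correlations with 18F-DOPA and fMRI.

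The cost is a few words in three places. The multilevel analysis is already planned, and no new data or larger sample is needed. The choice should be recorded before post-test diary data are compared between groups.
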